### Randomization and procedure

The study medication (omega-3 PUFA and placebo) will be provided by Marinex International Sp. z o.o. and shipped from Scandinavian Laboratories, Inc. Mt. Bethel, PA, USA. It will be sent to the store of the Central Teaching Hospital of the Medical University of Lodz, Poland, including a randomization code list and sealed envelopes for unblinding in case of a serious adverse event. Patients will be allocated the lowest available number of the randomization code list, and the Clinical Trial Store will dispense bottles of study medication according to the allocated number. Each bottle contains capsules of study medication, i.e. either 1320 mg/day of EPA plus 880 mg/day of DHA or an equal amount of an olive oil placebo. Both placebo and active capsules contain an antioxidant, i.e. 0.2% alpha-tocopherol (vitamin E). The placebo contains also a scant amount of fish oil to provide a comparable taste of the different capsules. The key to the randomization list will remain with Marinex International Sp. z o.o. until the last study participant completes the trial. Both the patients and the study staff responsible for study assessments will remain blind to the status of the patients throughout the study. Participants will be assessed by a registered dietician (ET) and advised to adhere to a balanced diet for the duration of the study.

### Interventions

#### Rationale for intervention arms

Early studies of red blood cell membranes in patients diagnosed with schizophrenia found deficiencies of both n-3 and omega-6 fatty acids, especially arachidonic acid (AA) and docosahexaenoic acid (DHA). Similar findings were found by post mortem studies of the frontal lobes of patients. The formulation of the Membrane Phospholipid Hypothesis of schizophrenia resulted in a number of double blind, placebo controlled intervention studies in patients with schizophrenia. Initial studies were quite small and were based on omega-6 PUFA, mainly gamma linoleic acid, and the results were generally negative [54]. Later, other n-3 PUFA were used in a series of intervention trials.

A double blind placebo-conntrolled study by Peet et al. [21] assessed the efficacy of add-on 12 week supplementation with 2 g/day EPA enriched oil, 2 g/day DHA enriched oil or a corn oil placebo in reducing the intensity of symptoms in patients with chronic schizophrenia. At the end of the trial, the PANSS score was significantly lower in the EPA-supplemented patients than in the placebo group. No significant differences were found between the DHA enriched oil group and the placebo group. The same group of researchers also tested the efficacy of 12-week supplementation with 2 g/d EPA enriched oil as a sole treatment for new or relapsed cases of schizophrenia who were not treated with antipsychotics. After a 3-month intervention period, the EPA-treated group had significantly lower PANSS scores than the placebo group. Moreover, significantly fewer EPA group patients required treatment with antipsychotics at the end of the study and the length of antipsychotic therapy was significantly shorter in the EPA supplemented group than the placebo corn-oil group.

Peet and Horrobin [24] followed up these early studies with a dose-ranging placebo-controlled study of 1, 2 or 4 g/day of ethyl-EPA or liquid paraffin-placebo as add-on therapy of chronic schizophrenia patients. The results indicate that a dose of 2 g/day of ethyl-EPA used for 12 weeks significantly reduced psychopathology in comparison with placebo but only in patients treated with atypical antipsychotic - clozapine. Doses of 1 and 4 g/day for 12 weeks were not found efficacious.

Three other teams of researchers have assessed EPA supplementation as add-on therapy in patients with chronic schizophrenia using double-blind placebo controlled trials. Fenton et al. [23] observed no significant differences in the PANSS scores of chronic schizophrenia patients treated with either mineral oil placebo or 3 g/day ethyl-EPA for 16 weeks. However, RBC membrane PUFA level significantly increased in both groups, which could suggest that the participants consumed n-3 PUFA rich food or supplements during the trial. Another trial by Emsley et al. [22] noted significantly higher reduction of PANSS scores in chronic medicated schizophrenia patients receiving 12-week interventions of 3 g/day of ethyl-EPA then those given paraffin oil placebo. The highest reduction was observed in patients treated with typical antipsychotics.

Negative findings have also been found in chronic schizophrenia patients. Norwegian researchers [55] report generally negative results for 2 g/day of ethyl-EPA, vitamin C (1000 mg/day) and vitamin E (364 mg/day) for 16 weeks as add-on therapy of psychotic exacerbation in chronic schizophrenia patients. The authors conclude that given separately during an acute episode, EPA and vitamins E + C increased the severity of psychotic symptoms in patients with low red blood cells (RBC) levels of PUFA. When combined, the effect of these agents on symptom severity was not significantly different from placebo. No significant effects were observed for combined EPA and vitamin C + E administration on PANSS score in high-RBC PUFA level individuals.

Negative findings were also reported for the effect of n-3 PUFA in first-episode schizophrenia patients. Another group of researchers [26] assessed the effect of 2 g/day of ethyl-EPA add-on therapy carried out for 12 weeks on symptom severity in early psychosis. The study results did not demonstrate a sustained symptomatic benefit of ethyl-EPA in early psychosis, but ethyl-EPA was able to accelerate treatment response and improve the tolerability of antipsychotic medications. The authors argue that a ceiling effect may have been responsible for the negative results of the study, since a high proportion of first-episode patients already achieve symptomatic remission with antipsychotic medication alone.

Finally, n-3 PUFAs were assessed in individuals at ultra-high risk (UHR) of psychosis. A randomized placebo-controlled clinical trial by Amminger at al [56] indicates that 12-week supplementation with 1.2 g/day n-3 PUFA (i.e. 700 mg of EPA and 440 mg/day of DHA) is effective in preventing transition to full-threshold psychosis in UHR individuals.

To sum up, the results of clinical trials of n-3 fatty acid supplementation in chronic schizophrenia are inconsistent. EPA was mainly used in the trials. The majority of positive results were obtained with 12-week EPA supplementation at daily doses of 2 and 3 g [21,22,24]. DHA alone was used in one study conducted by Peet [21] and the results were negative. One study based on first-episode schizophrenia did not identify any positive effects of EPA on psychopathology, possibly due to the ceiling effect [26]. A 12-week supplementation with 1.2 g/daily of EPA + DHA was found efficacious in preventing transition to full-threshold psychosis in individuals with clinical high risk of schizophrenia development [56].

The rationale for using EPA supplementation to study efficacy in early schizophrenia and relapse prevention is mainly based on the findings of the chronic schizophrenia studies described above. The observation that EPA + DHA add-on therapy could prevent psychotic disorder development in UHR individuals supports an intervention comprising both EPA and DHA. The rationale for using DHA supplementation is based mainly on evidence accumulating from basic, animal and human studies, indicating that the DHA molecule has unique structural properties which appear to provide optimal conditions for a wide range of cell membrane functions. This has particular implications for grey matter, which is membrane-rich tissue and abundant in DHA. A recently identified important metabolic role played by DHA is the precursor for resolvins and protectins, both of which have anti-inflammatory properties [57] and provide neuroprotection against oxidative stress and apoptosis [58]. Oxidative stress and neuroinflammation has long been implicated in the pathogenesis of schizophrenia. Since poor cognitive function was found to be a risk factor for relapses of schizophrenia, it is significant that it can be influenced by DHA. DHA was found to improve cognition in healthy individuals [59,60] and in animal models [12,61], it has been found to be involved in neurogenesis and neuroplasticity [62] and is thought to be essential for neurodevelopment [48].

EPA and DHA supplementation was found to be efficacious in an open label study of schizophrenia patients treated with haloperidol [63]. Only one study addresses the efficacy of n-3 PUFA administration in reducing relapse rate in schizophrenia [43]. An intervention based on 2 g of EPA plus 1 g of DHA and 300 mg of antioxidant alpha-lipoic acid daily was used as the sole treatment in stable schizophrenia patients whose antipsychotic therapy was discontinued according to the current guidelines. The results of the study were negative. No significant differences in relapse rate were found between the active and placebo groups.

It is intended to use an intervention based on EPA and DHA at a ratio of 1.5:1 by weight in the proposed OFFER study. This form of intervention has not been used so far in first-episode schizophrenia patients. In addition, trials using only EPA supplementation have returned inconsistent findings, and the RCT carried out by Amminger et al. discussed above has already demonstrated the efficacy of EPA + DHA in reducing the risk of conversion to psychosis in individuals at ultra-high risk. Hence, an OFFER study based on a long-term intervention comprising both EPA and DHA as add-on therapy appears to offer a great deal of potential.

### Doses

The study participants will be supplemented with 1320 mg/day of EPA and 880 mg/day of DHA. Higher doses of EPA and DHA will be used in the OFFER trial than in the study led by Amminger et al., who assessed transition to psychosis in individuals with high clinical risk. It is assumed that the higher level of psychopathology present in first episode schizophrenia patients reflects higher PUFA metabolic abnormalities, which require higher doses of n-3 PUFA for normalization. The doses of EPA and DHA intended to be used in the present study have been found to be well tolerated and safe in earlier studies of patients diagnosed with schizophrenia [21].

### Control condition

Olive oil was chosen as placebo because it contains mainly monounsaturated fatty acids and only small amounts of unsaturated and polyunsaturated fatty acids. Previous studies used placebo composed of liquid paraffin [22,24] and coconut oils [56], which are composed mainly of unsaturated fatty acids. Since one of the secondary outcome measures in the OFFER study was a change in the metabolic profile, an oil with low unsaturated fatty acid content was chosen in order to avoid bias. As the corn oil used in previous studies [21] contains large quantities of omega-6 PUFA which negatively influences n-3 PUFA metabolism, it could influence the main outcome by increasing the effect of the intervention. However, since olive oil contains relatively small amounts of linoleic acid (20:4, omega-6), and the fact that it is a common constituent of the Polish diet, it is a more suitable placebo. In addition, its familiarity as an ingredient has two further benefits: firstly, it could reduce the risk of not giving consent, thus facilitating recruitment by reducing patient concerns, and secondly, it may reduce the non-compliance and attrition rates in the study. Moreover, it could be unethical to use placebo composed of mainly monounsaturated fatty acids in FES patients, who are at risk of developing hyperlipidemia, especially when treated with second generation antipsychotics.

### Duration of intervention

The intervention period in the majority of the previous studies assessing the efficacy of n-3 PUFA in schizophrenia lasted 8 to 12 weeks. No longer term trials were conducted. The present study is planned to last 52 weeks and will be composed of two phases: intervention and follow-up. The intervention period is designed to be continued for 26 weeks. Participants will be observed for the 26 weeks following the intervention phase.

### Medication adherence

For all patients, parent/patient self-report adherence data will be collected regarding intervention and all psychotropic medications at each medication visit. For participants receiving study medication (i.e., n-3 PUFA or placebo), information will also be collected by pill count at all medication appointments.

### Clinical outcome measures

#### Measures and assessment of outcomes

Clinical scales will be used to assess several domains of symptoms and patient functioning. The severity of schizophrenia symptoms will be measured using the Positive and Negative Syndrome Scale [64], which is composed of 30 items scored 1–7, with a total score ranging from 30, indicating an absence of psychopathology, to 208. PANSS is a reliable and valid scale commonly used to score symptom severity in schizophrenia [65].

Depressive features will be measured by the Calgary Depression Scale for Schizophrenia (CDSS) that was developed specifically for schizophrenia patients [66]. It is an observer-rated scale consisting of 9 items, each with 4 anchor points. The validity and reliability of the scale was assessed in adults [67] as well as in adolescents [68].

Patient functioning status will be measured by means of Global Assessment of Functioning (GAF) scale. The GAF is a method for representing a clinician’s judgment of a patient’s overall level of psychosocial functioning [69]. The GAF requires a clinician to make an overall judgment about a patient’s current psychological, social, and occupational functioning. In the DSM-IV, this rating is given on a scale from 1 to 100, with ratings of 1 to 10 indicating severe impairment and ratings of 91 to 100 indicating superior functioning.

The Clinical Global Impressions scale will be used to measure symptom severity (CGI-S) and the range of improvement (CGI-I). CGI-S and CGI-I scales are commonly used to assess efficacy of treatment in patients with mental disorders [70]. The level of insight will be assessed with the “My thoughts and feelings” questionnaire, which was validated in population of Polish patients with schizophrenia [71].

All the raters have undertaken intensive training in the scoring methods used in the study as part of the first Polish program for people at high clinical risk of psychosis development (PORT), which is described in detail elsewhere [72]. The raters achieved good reliability scores (coefficient of agreement >0.82) and were all within 20% of the standard scores.

### Primary outcome measure

The primary outcome measure will be the efficacy of n-3 PUFA in reducing psychopathology in first-episode schizophrenia. The Positive and Negative Syndrome Scale [64] will be used to assess the efficacy of EPA + DHA supplementation in reducing symptom severity in first-episode schizophrenia after 8 and 26 weeks of supplementation. The main outcome measure will be the change in symptom severity from baseline to week 26. Baseline PANSS total score will be subtracted from PANSS score obtained after 26 weeks, resulting in the degree of change observed in the study.

Another way of assessing the efficacy of n-3 PUFA in reducing symptom severity in first-episode schizophrenia patients will be the comparison of the number of responders in each intervention group: 25% and 50% decreases in PANSS total score are considered cut-offs for clinically significant symptom reduction and indicates minimal and great improvement [73]. The percentage change of scores will be calculated according to Leucht et al. [73], based on the principle that a patient with no psychopathological symptoms scores 1 in all PANSS scale items. The formula for calculating change will be as follows: [(Pt2 – N) – (Pt1 – N)/(Pt1 – N)]•100, where Pt1 is the PANSS subscale score at the beginning of the study, Pt2 is the value at the end of the study and N is the number of PANSS subscale items. N = 7 for PANSS positive and negative subscales, N = 16 for the general psychopathology PANSS subscale and N = 30 for the total PANSS score. Patients who achieve at least a 25% reduction in the total PANSS score will be regarded as responders. Those who achieve a 50% decrease will be regarded as much improved.

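### The PANSS percentage-change formula is bracketed wrongly: as printed it ignores baseline and cannot yield the 25% and 50% response cut-offs

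*Protocol article*

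**What the plan says.** In the Protocol article, the section Primary outcome measure first fixes the main outcome as the simple change in PANSS total from baseline to week 26. It then adds a comparison of the number of responders per arm, based on a percentage change calculated by a cited published method, "based on the principle that a patient with no psychopathological symptoms scores 1 in all PANSS scale items".

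The formula is announced with "The formula for calculating change will be as follows" and printed in full: "The formula for calculating change will be as follows: [(Pt2 – N) – (Pt1 – N)/(Pt1 – N)]•100". The terms are defined next: "Pt1 is the PANSS subscale score at the beginning of the study", and "Pt2 is the value at the end of the study and N is the number of PANSS subscale items". N is 7 for the positive and negative subscales and 16 for general psychopathology, with "N = 30 for the total PANSS score".

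The classification follows: "Patients who achieve at least a 25% reduction in the total PANSS score will be regarded as responders". The higher category is "Those who achieve a 50% decrease will be regarded as much improved". The article gives no other version of the formula.

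**The concern.** The stated aim is a percentage change from baseline after removing the one point per item that a symptom-free patient still scores. That requires the whole difference between the two floor-corrected scores to be divided by the floor-corrected baseline. In the printed expression no bracket groups that difference as a numerator. By the usual order of operations, the division applies only to the last two terms.

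This is the article's only operational rule for who counts as a responder or as much improved. If it were programmed as printed, nearly all true responders would be lost from both arms and the responder comparison would tell the reader almost nothing.

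**Working it through.** **Inputs**
- Formula, definitions of Pt1, Pt2 and N, and cut-offs: Protocol article, Primary outcome measure.
- Minimum total score of 30 (30 items scored 1 to 7): Protocol article, Clinical outcome measures.
- Baseline above the minimum (Pt1 > N): assumed, because Participant sample requires patients to be currently psychotic.
- Baseline total score: not given. I assume 90 for illustration and 60 to 120 as a range.

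**Step 1: the formula as printed.** For any Pt1 > N, (Pt1 − N)/(Pt1 − N) = 1. The expression is therefore [(Pt2 − N) − 1] × 100 = (Pt2 − N − 1) × 100, and Pt1 has dropped out.

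**Step 2: who reaches the cut-offs as printed, N = 30.** A reduction of at least 25% means a result of −25 or lower:
- (Pt2 − 31) × 100 ≤ −25 requires Pt2 ≤ 30.75.
- (Pt2 − 31) × 100 ≤ −50 requires Pt2 ≤ 30.5.

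PANSS totals are whole numbers of at least 30, so both conditions mean Pt2 = 30, where the result is −100%. At Pt2 = 31 the result is already 0%. The two response categories therefore coincide. On the subscales, likewise, only Pt2 = 7 (positive, negative) or Pt2 = 16 (general) qualifies.

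**Step 3: the intended form.** Percent change = 100 × [(Pt2 − N) − (Pt1 − N)]/(Pt1 − N).

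**Step 4: the two forms side by side, N = 30, assumed baselines**

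| Baseline | End | As printed | Re-bracketed |
|---|---|---|---|
| 60 | 45 | +1400% | −50% |
| 70 | 50 | +1900% | −50% |
| 80 | 55 | +2400% | −50% |
| 90 | 60 | +2900% | −50% |
| 100 | 65 | +3400% | −50% |
| 120 | 75 | +4400% | −50% |
| 90 | 75 | +4400% | −25% |
| 90 | 90 | +5900% | 0% |
| 90 | 30 | −100% | −100% |

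For 90 to 60, as printed: (60 − 30) − (90 − 30)/(90 − 30) = 30 − 1 = 29, and 29 × 100 = 2900. Re-bracketed: (30 − 60)/60 × 100 = −50.

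**Step 5: direction of the error.** Take every whole-number pair with baseline 31 to 210 and end score 30 to 210 (210 = 30 × 7), which is 180 × 181 = 32,580 pairs.
- As printed, 180 pairs are responders, all with Pt2 = 30.
- Re-bracketed, 12,330 pairs are responders, and they include those 180.
- So 12,330 − 180 = 12,150 pairs change class (12,150/32,580 = 37%), every one a lost responder.

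These are counts of possible score pairs, not expected patient frequencies. The article prints 208 as the upper limit of the total, but the result in Step 2 does not depend on the upper limit.

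**The case against.** The strongest reply is that nobody would be misled. The same paragraph names a percentage change, cites a published method, states the floor-correction principle, gives N for each scale and sets cut-offs at 25% and 50% reductions. Only one placement of brackets fits all of that. An analyst who saw +5900% for an unchanged patient would stop at once. This stands, and it limits the practical risk. It does not make the printed rule correct.

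A second reply is that a stacked fraction may have been flattened when the text was read from PDF. This cannot be fully excluded. It looks unlikely, because the slash is printed inline and the brackets are balanced.

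A third reply is that the formula carries little weight. This also stands. The main outcome is a simple difference analysed by ANCOVA, and the Power calculation section does not refer to responders.

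A reader might go further and infer that every classification would be wrong. The arithmetic does not support that: true non-responders remain non-responders and patients ending at 30 remain responders. Nor is +2900% a general result, since it belongs to an assumed baseline of 90. The use of the word subscale in the definitions is not a fault either, because the text gives N for the total score and the responder rule names the total.

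**Conclusion.** The formula is wrong as written. For any baseline above the scale minimum it equals (Pt2 − N − 1) × 100, ignores baseline and cannot produce the stated cut-offs. On the total score only an end value of exactly 30 would count as response, and it would count as much improved too. The error runs one way: true responders are lost and no false ones are created.

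The algebra needs no assumption beyond Pt1 > N and the ordinary order of operations. The size of the example figures does depend on assumed baselines: a true 50% reduction comes out at +1400% to +4400% for baselines of 60 to 120.

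The effect is confined to the supplementary responder comparison. A reader might infer that the primary result is compromised, but the article does not support this, because the change in PANSS total to week 26 does not use the formula. The relapse criterion of a 25% rise in PANSS total does not refer to the formula either, so the finding is not extended to it.

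**What to change.** Print the formula with the whole difference as numerator:

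percent change = 100 × [(Pt2 − N) − (Pt1 − N)]/(Pt1 − N), which simplifies to 100 × (Pt2 − Pt1)/(Pt1 − N).

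State the sign convention with it: on the total score (N = 30), responder if the result is −25% or lower, much improved if it is −50% or lower. One worked case, such as 90 to 60 giving −50%, would let a programmer check the code.

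The cost is one corrected line. The design, sample size, data collection and main analysis do not change.

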### The first secondary aim

The secondary aim of the study is to assess whether 26 weeks intervention with 2.2 g of marine long-chain n-3 polyunsaturated fatty acids initiated in the acute phase of first episode schizophrenia can prevent relapse during one year observation. Schizophrenia relapse will be operationally defined as meeting any of one or more of the following specified individual criteria given by Csernansky et al. [74]: (a) a 25% increase in PANSS total score; (b) deliberate self-injury; (c) emergence of clinically significant suicidal or homicidal ideation; or (d) violent behavior resulting in significant injury to another person or significant property damage; (e) admission to psychiatric inpatient clinic due to exacerbation. Since no common agreement exists regarding the relapse criteria, the most commonly used criteria were chosen on the basis of a recent meta-analysis [75]. The presence of relapse will be assessed during all study visits except for the first. The chosen study design concerning relapses is more pragmatic than explanatory and is used to reflect the frequent clinical observation that patients treated for first-episode schizophrenia achieve partial symptomatic remission with persistence of certain symptoms after the acute phase of the illness.

